### Step 6: Evaluation plan

#### Study design

The intervention as developed in the previous steps will be evaluated in a cluster-randomised controlled trial in South African worksites with a 12-month follow-up. The two intervention groups will receive 6 counselling sessions over either a 3 or 6-month period, described in Table 3. The control group will receive usual care. These participants will be unaware of the other two groups participating in the research study.

**Table 3 T3:** Timeline and contact schedule for employees in the intervention groups

**Week**	**6-month intervention group**	**3 month intervention group**
0	Wellness day at company. (Baseline measurement)	Wellness day at company. (Baseline measurement)
1	Face-to-face contact	Face-to-face contact
	(set goals, action plan)	(set goals, action plan)
4	Telephone contact	Telephone contact
	(monitor progress)	(monitor progress)
8	Telephone contact	Telephone contact
	(monitor progress)	(monitor progress)
12	Telephone contact	Face to face (final contact)
	(monitor progress)	
16	Telephone contact (monitor progress)	
20	Telephone contact	
	(monitor progress)	
24	Face to face (final contact)	
	(set new goal, plan way forward)	
26	First follow up measurement	
52	Second follow up measurement	First follow up measurement Second follow up measurement

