#### Setting

The study will be conducted in cooperation with a major national private health insurer, Discovery Health. Large companies (>300 employees) that are clients of this insurer, offering health and wellness days and that are based in three South African cities will be eligible to participate in this study.

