#### Randomisation

Randomisation will take place at the company level, where participating companies will be assigned to either the intervention or the control group. The wellness specialists’ manager will assign each company with a number and then use a random numbers table to allocate the companies to either the intervention or control.

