#### Sample size calculation

The sample size was determined according to a power calculation using a dichotomous variable: meeting the PA guideline with at baseline 50% not meeting the guideline and after the intervention 40% (intervention group) vs 50% (in control group). Based on these numbers, and 80% power and significance of 0.05, 775 employees are required at the 12-month follow-up with 387 in control group and 387 in intervention group. Thus, assuming that approximately 20% of participants will be lost to follow-up at 12 months, we will aim to recruit 928 employees at baseline and allocate 424 to the intervention and control groups (Figure 1).

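### As described, companies are allocated by simple randomisation, which fixes neither the number per arm nor the balance by city or company size; the risk is material if only about 6 to 12 companies take part

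*Protocol article*

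**What the plan says.** The unit of allocation is clear from the Randomisation section: "Randomisation will take place at the company level, where participating companies will be assigned to either the intervention or the control group". The same section gives the method. The wellness specialists' manager numbers each company and will then "use a random numbers table to allocate the companies to either the intervention or control". No block, quota, stratum, matching or minimisation is mentioned there or elsewhere in the article.

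The Setting section describes the clusters. They are "Large companies (>300 employees) that are clients of this insurer", they offer wellness days, and those "based in three South African cities will be eligible to participate in this study". There is no upper limit on size. The number of companies is not given.

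The Sample size calculation section works in employees. It needs 775 at 12 months, with "387 in control group and 387 in intervention group".

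**The concern.** City and company size could plausibly be related to activity, diet, health claims and absenteeism. Simple randomisation balances such factors only on average over many units. When the units are companies and there are few of them, one draw can leave the arms with quite different numbers of companies, or place every company from a city in the same arm. The comparison between arms is then partly a comparison between cities, and little can be done about it afterwards. An uneven split also loses precision. Both risks can be reduced or removed at the time of the draw for almost nothing, so it matters which method the plan commits to.

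**Working it through.** **1. The plan's own figure.** Inputs from the Sample size calculation section: 50% against 40% not meeting the activity guideline, 80% power, significance 0.05 (taken as two-sided), equal groups. With the pooled-variance formula and no continuity correction:

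n = [1.96 × √(2 × 0.45 × 0.55) + 0.8416 × √(0.50 × 0.50 + 0.40 × 0.60)]² / 0.10² = (1.379 + 0.589)² / 0.01 ≈ 387.3 per group, or about 775 in total.

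The stated 387 and 775 are reproduced. Power at 387 per group is 79.97%.

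**2. Number of companies, k.** This is not in the document and has to be assumed. If each company supplied about 100 participants, 928 / 100 gives about 9 companies. At about 30 each, 928 / 30 gives about 31. The range 6 to 30 is used below.

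**3. Number of companies per arm.** Under simple 1:1 allocation the number in one arm is Binomial(k, 0.5). For k = 12, a split of 4:8 or worse has probability 2 × (1 + 12 + 66 + 220 + 495) / 4096 = 1588 / 4096 = 0.388. For k = 6, 2:4 or worse is 2 × (1 + 6 + 15) / 64 = 0.688.

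**4. A city wholly in one arm.** Assume the companies are spread as evenly as possible over the three cities. A city with m companies falls wholly in one arm with probability 2 × 0.5^m. For k = 12 (4 per city), the chance that this happens to at least one city is 1 − (1 − 2/16)³ = 0.330. For k = 6 (2 per city), it is 1 − (1 − 2/4)³ = 0.875.

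**5. The same with arm totals forced equal.** For k = 12 there are C(12, 6) = 924 equal splits. Those with no city wholly in one arm number 6³ + 6 × (4 × 6 × 4) = 216 + 576 = 792, which leaves 132 / 924 = 0.143.

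| k | Split of 2:1 or worse, simple | At least one city wholly in one arm, simple | Same, equal arm totals |
|---|---|---|---|
| 6 | 69% | 88% | 60% |
| 8 | 29% | 72% | 49% |
| 10 | 34% | 51% | 29% |
| 12 | 39% | 33% | 14% |
| 20 | 11.5% | 6% | 1.6% |
| 30 | 10% | 0.6% | 0.1% |

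Fixing the arm totals alone does not solve the city problem when k is small. Blocking within city, with at least two companies per city, brings the last column to zero.

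**6. Cost of an uneven split.** Suppose 774 employees divide 2:1, as 258 and 516. The pooled proportion is (258 × 0.50 + 516 × 0.40) / 774 = 0.433. The null standard error is 0.0378 and the alternative standard error 0.0379. Then z = (0.10 − 1.96 × 0.0378) / 0.0379 ≈ 0.685, and power is 75.3%, against 80% with equal groups. No clustering penalty is included in either figure.

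For the between-company component with equal-sized companies, a 4:8 split multiplies the variance of the arm difference by (1/4 + 1/8) / (1/6 + 1/6) = 1.125.

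**7. Cost of adjusting for city.** In a company-level analysis with 6 companies and two arms there are 4 degrees of freedom, and the two-sided 5% critical t is 2.78. Two city terms leave 2 degrees of freedom, and the critical value becomes 4.30.

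**The case against.** The strongest reply is that the article does not say allocation is unrestricted. A random numbers table is only a source of randomness. It can be used within strata, or to draw a fixed half of a numbered list, and a condensed article may leave that to the full protocol. This stands as a caution: restricted allocation cannot be ruled out. It does not dispose of the point, because the article gives a concrete procedure, and someone following it as written would carry out simple randomisation.

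The second reply is that a small number of clusters is an inference. Yield per company is filtered by voluntary attendance at the wellness day, by the risk or obesity criterion, by consent and by contract length. Thirty or more companies are possible, and a whole-city confound is then negligible. This stands, and the finding is conditional on k for that reason.

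Some stronger readings are tempting but not supported:

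- **A clash with the sample size.** A reader might infer that the equal groups of 387 contradict the allocation method. They count employees, not companies. Unequal company numbers need not prevent equal recruitment, and equal company numbers would not guarantee it.
- **Bias.** Chance imbalance under proper randomisation is not systematic bias. The primary outcome is a change from a measured baseline, which partly removes stable differences between companies or cities.
- **City-based counsellors.** The article places counsellors in three cities only for the pilot study, so confounding of city with counsellor in the trial is not established.
- **Three arms.** The Study design section says "The two intervention groups will receive 6 counselling sessions over either a 3 or 6-month period", while the Randomisation section describes a two-way allocation. Any three-way split would leave fewer companies per group, but the article does not say how companies are divided between the two schedules, so no figure is put on it.

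**Conclusion.** The point holds in conditional form. The allocation method as described contains no device to fix the number of companies per arm or to balance city or company size. If about 6 to 12 companies take part, serious imbalance is a realistic outcome: a 29% to 69% chance of a 2:1 or worse split, and 33% to 88% for a city wholly in one arm. At 20 companies the concern is modest. At 30 the city problem all but disappears, although about a 10% chance of a 2:1 or worse split remains.

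The consequence is lost precision and a less credible comparison. On nominal power alone it is about 5 percentage points for a 2:1 split of employees. These figures assume simple 1:1 allocation between two arms and, for the city figures, companies spread nearly evenly over the three cities. The article states neither the number of companies nor their spread.

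**What to change.** State the number of companies. List all committed companies before the draw, then allocate them in one step with a fixed number per arm. Use blocks within city, or constrained randomisation over the set of acceptable allocations, balancing city and company size as far as the number of companies allows. Reflect the restriction in the analysis, but adjust for city only if enough companies are enrolled to spare the degrees of freedom.

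This needs no extra participants or data, only a short randomisation program in place of a printed table. Much of the groundwork is already planned: companies provide letters of commitment (Inclusion and exclusion criteria for companies) and are numbered before allocation (Randomisation). There are two real costs. The list must be complete before the draw, so late-joining companies are harder to accommodate. Adjusting for city uses up to two company-level degrees of freedom, which is material with very few companies. With about six companies, balancing on both city and size may not be fully achievable, and the plan should then say which factor takes priority.

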#### Blinding

Due to the nature of the research, the wellness specialists will not blinded and knew which companies were receiving the intervention. However, the employees participating in the research study were not aware of the expected outcomes of the study, nor were they aware of the other (either control or intervention) group participating in the research study.

#### Inclusion and exclusion criteria for companies

Companies with 300 or more employees will only be selected from those willing to allow a repeat of the HRA onsite at 6 and 12 months follow-up. In addition, the employer should have employee absenteeism data from their employee records available.

One of the challenges with worksite health promotion programs is that the company management should “buy in” to the intervention and support its implementation, and also “buy in” to the study and be willing to being placed in the wait-list control arm of the study. These issues will be discussed with the company during recruitment. To emphasize the importance of continued support, we require a letter of commitment from the management of prospective companies for the duration of the study. Furthermore, the researchers will invite participation and seek approval from the respective unions and health and safety committees functioning at the companies.

#### Inclusion and exclusion criteria for employees

Employees identified to be at ‘increased’ or ‘high’ risk for cardiovascular disease are eligible to take part in the research study. Risk status will be determined by using an adapted Framingham Score [18] together with habitual physical activity levels, and Body Mass Index. This score incorporates age, total cholesterol, blood pressure and smoking status and ranks individuals according to their level of risk, ranging from very low to very high 10-year risk of fatal CVD . Those members presenting for health risk appraisal with a risk of 10% or higher will be considered eligible. Independent of risk status, those employees who are obese (Body Mass Index > 30 kg/m2) also will be eligible to take part in the study. Only those employees who are include18 years or older and who have a contract with employer until end of 12-month measurement period will be invited to participate.

Employees will be excluded for the following reasons: pregnancy, diagnosis or treatment of cancer, any other disorder that makes physical activity impossible. Contract workers whose employ with the company will end before the 12 month follow up measurement, will also be excluded from the study.

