Increase fruit and vegetable intake.	8. Employees aim to accumulate at least 30 minutes of physical activity on at least 5 days of the week.
	8. Employees aim to increase daily fruit and vegetable intake to 5 servings or more per day.
	9. Employees list and choose a variety of fruit and vegetables that they might enjoy.
	10. Employees develop strategies and ideas with the wellness specialist to prepare their food/meals (and not to buy fast food/take out meals).

The work environment also inhibited physical activity, as employees spent most of their time sitting. One environmental barrier identified was seasonality, as employees interviewed indicated that they would not be prepared to exercise outdoors during the winter months, when the sun set earlier. Employees felt that they generally followed healthier diets during summer, when their intake of salads was higher, and there was a greater variety of fruit and vegetables.

Thus, the main objectives of the intervention are to increase habitual levels of moderate and vigorous intensity physical activity (to meet guideline of 150 minutes per week) and to improve dietary behaviour, specifically increased fruit and vegetable intake. The reduction in the totalnumber of risk factors will play a role in achieving the long-term goal of reduced risk and burden of cardiovascular disease.

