#### Study population

Over the course of two months, all employees from the eligible companies will be invited to participate in the wellness day(s) of their company. The health insurer will offer and conduct a Health Risk Assessment of risk factors, including: family history, Body Mass Index (BMI) and body fatness, blood pressure and finger-prick cholesterol and glucose concentrations, self-report physical activity and dietary intake behaviour, smoking, and stress, to the employees at the wellness day.

Those employees who are identified to be at ‘increased’ or ‘high’ risk for CVD, based on an adapted Framingham score of 10% or more [18] will be invited by the wellness specialists (via telephone call) to take part in the research study. Employees agreeing to participate will be asked to sign an informed consent and to provide their email address and contact details.

Because all the companies hosting wellness days in this research study are clients of a major national health insurer, it will be able to access data for employees who do not volunteer for the screening activities, and thus be able to compare responders to non-responders. Recorded data for all employees include healthcare expenditure and whether they participated in a health screening activity recently. The data for the employees who choose not to participate will be sent to the researchers without any personal identifiers, thus ensuring employee confidentially. Being able to describe the non-responders is one of the strengths of this study design, and the insured population with whom we are working, providing insight into the problem of selection bias.

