### Habitual physical activity

Habitual physical activity will be measured using the ‘Global Physical Activity Questionnaire’ (GPAQ) [31]. This is a self administered questionnaire that includes questions on habitual levels of light, moderate and vigorous activity. The physical activity domains include work-related activity, transport and leisure time activity, which are then summed to calculate total minutes of physical activity per week. Participants will be categorised according to whether they meet the American College of Sports Medicine guideline of 150 minutes of physical activity per week.

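### The trial is sized on a single follow-up proportion meeting the activity guideline that takes no account of baseline status, although entry sets no activity cut-off and half are assumed to meet the guideline already; adjusting for baseline status is a free improvement.

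*Protocol article*

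**What the plan says.** All references are to the protocol article.

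- **Objective** (Step 2: Defining performance objectives). A main objective is "to increase habitual levels of moderate and vigorous intensity physical activity (to meet guideline of 150 minutes per week". Improving diet is the other.
- **Entry** (Inclusion and exclusion criteria for employees). The risk route is "Those members presenting for health risk appraisal with a risk of 10% or higher will be considered eligible". The second route is "Independent of risk status, those employees who are obese (Body Mass Index > 30 kg/m2) also will be eligible". On the score itself: "This score incorporates age, total cholesterol, blood pressure and smoking status". The Study population section invites employees "based on an adapted Framingham score of 10% or more".
- **Activity in the entry rule** (same criteria section). Activity is mentioned once: "Risk status will be determined by using an adapted Framingham Score [18] together with habitual physical activity levels, and Body Mass Index". No cut-off follows, and neither route is made to depend on inactivity.
- **Sizing** (Sample size calculation). The variable is yes/no, meeting the guideline, with "at baseline 50% not meeting the guideline and after the intervention 40% (intervention group) vs 50% (in control group" not meeting it. At 80% power and 5% significance this gives 775 employees at 12 months, 387 per group.
- **Measurement** (Habitual physical activity). "Participants will be categorised according to whether they meet the American College of Sports Medicine guideline of 150 minutes of physical activity per week".
- **Primary outcome** (Outcome measures). This is worded more broadly, as a change in the level of habitual daily physical activity.

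**The concern.** An obese employee who reports 300 min/week is eligible. On the guideline outcome that person can only stay above the line or fall below it. By the sample size section's own figure, half of those enrolled start in that position.

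A single follow-up proportion over everyone then mixes two different things: insufficiently active employees reaching the guideline, and active employees keeping to it. If counselling works mainly on the first, the overall 10 points stand for a much larger change in that half, and the sample size section does not say so. A moderate effect in the employees whom the activity objective most concerns could be missed. Baseline guideline status is a plausible strong predictor of follow-up status and is collected anyway, so leaving it out of the comparison gives up precision.

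**Working it through.** **Inputs from the protocol article.** Not meeting the guideline: 50% at baseline; 50% (control) and 40% (intervention) at follow-up; 387 per group; 80% power; 5% significance, taken as two-sided because sidedness is not stated. Pilot activity: mean 63.0 min/week, SD 120.9 (Table 2).

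**Assumptions, not in the article.** A share x of each baseline category switches spontaneously by 12 months, with x = 10%, 20% or 30%. Equal switching keeps the control group at the planned 50%. Clustering is left out throughout, as no intracluster correlation is given. The powers below are therefore for comparison with one another and are not the trial's actual power.

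**1. The plan's own figure.** With z = 1.96 and 0.8416:
- Pooled variance: n = [1.96·√(2·0.45·0.55) + 0.8416·√(0.25 + 0.24)]² / 0.10² = 387.3 per group. Twice that is 774.7, so 775 in total. The figure reproduces.
- Unpooled variance: n = (0.25 + 0.24)(1.96 + 0.8416)² / 0.10² = 384.6, so 385. Power at 387 per group is 80% either way.

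**2. Implied effect below the guideline.** If only baseline non-meeters respond, the overall difference is 0.50 × effect. Hence effect = 0.10/0.50 = 20 points net. With switching x, non-meeters still below the guideline at follow-up are 1 − x (control) against 0.8 − x (intervention): 90 v 70%, 80 v 60% or 70 v 50%.

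**3. If the true effect in non-meeters is 10 points.** The overall contrast is 50% v 45%. Power at 387 per group is about 29%, and 1,565 per group would be needed for 80%.

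**4. Is the 50% secure?** Minutes cannot be negative, so in a sample like the pilot the share at or above 150 is at most 63.0/150 = 42%. At least 58% would then be below the guideline, and the implied effect would be at most 0.10/0.58 = 17 points. The pilot was a convenience sample, so this is only indicative.

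**5. Three ways to analyse the same participants.** Each group has 387/2 = 193.5 people per baseline category. The stratified estimate weights the two within-category differences by one half each. Its variance is 0.25·(V₁ + V₂)/193.5, where V₁ and V₂ are the sums of p(1 − p) over the two groups among non-meeters and meeters. Power is Φ(d/SE − 1.96).

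Example, only non-meeters respond, x = 20%: V₁ = 0.16 + 0.24 = 0.40; V₂ = 0.16 + 0.16 = 0.32; SE = √(0.25 × 0.72/193.5) = 0.0305; power = Φ(0.10/0.0305 − 1.96) = 91%.

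| Where the effect acts | Whole sample, unadjusted | Whole sample, stratified (x = 10/20/30%) | Baseline non-meeters only (x = 10/20/30%) |
|---|---|---|---|
| 20 points, non-meeters only | 80% | 98 / 91 / 84% | above 98% throughout |
| 10 points in both categories | 80% | above 99 / 94 / 87% | 79 / 63 / 54% |
| 10 points, non-meeters only | 29% | 56 / 39 / 32% | 79 / 63 / 54% |

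The stratified whole-sample comparison beats the unadjusted one in every row. The subset analysis gains when only non-meeters respond. It is no better, and usually worse, than the unadjusted comparison when both categories respond.

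**The case against.** The strongest reply is that nothing here is an error. The 50% and 40% are whole-sample rates, so already-active employees are counted in the 387 per group. The target population is employees at increased cardiovascular risk, not inactive employees, and diet, body mass index and risk profile are outcomes too. An effect measured over that population is the effect in that population. All of this stands.

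Active employees are also not idle in the comparison. The final counselling session covers maintaining healthy behaviour (Motivational interviewing section), so prevented lapses are a legitimate part of the effect. The 20-point figure follows only if the effect is confined to non-meeters, which the article nowhere says. On the declared primary outcome, change in activity level, someone at 300 min/week can still improve. These points stand as well, and they confine the concern to the guideline outcome used for sizing.

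A reader might take the sentence naming habitual activity as part of risk status to mean that active employees are screened out. The text does not support that: it gives no threshold, the score does not contain activity, and the obesity route applies independently of risk status. If it did mean that, the 50% baseline assumption would not fit.

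Finally, the final model for the guideline proportion may properly sit in an analysis plan that is not shown. The absence of a model is therefore not held against the article. The point concerns the comparison that the sample size section does fix.

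**Conclusion.** The point holds in limited form. Entry sets no activity cut-off, half are assumed to meet the guideline at baseline, and the sizing contrast takes no account of who they are. If only those below the guideline respond, the planned 10 points mean a net 20 points among them, or at most about 17 if the pilot's activity level carries over. Using baseline status lifts the comparison from 80% to about 84–98% power in that case, and to about 87–99% if both halves respond equally. This rests on the assumed 10–30% switching and leaves out clustering.

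Three stronger readings are tempting and are not supported:
- **That the sample size is miscalculated.** It reproduces.
- **That half the sample carries no information, or that the result would appear at half its true size.** Prevented lapses count, and a whole-sample effect reported as such is not distorted.
- **That the guideline outcome should be restricted to employees inactive at baseline.** That is a trade-off: with a 10-point effect in both halves, power would be 79%, 63% or 54% instead of 80%.

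This is a free improvement, not a flaw that threatens the trial.

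**What to change.** Keep enrolment and the whole-sample guideline comparison at 12 months as they are. Then:

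1. Adjust or stratify that comparison by whether the participant met 150 min/week on the baseline wellness-day questionnaire, in a model that also allows for clustering by company.
2. Pre-specify, as a supporting result, the proportion reaching 150 min/week at 12 months among those below it at baseline. It should accompany the whole-sample outcome and not replace it.
3. State next to the sample size what the 10-point difference implies for those below the guideline, and say what role habitual activity plays in the definition of risk status.

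Table 3 places the baseline measurement at week 0 and the first counselling session at week 1, so the status is recorded before counselling starts and needs no new data. The cost is a little more analysis work. The supporting result should be read with its smaller numbers in mind: about 193 per group if half are below the guideline.
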